## Methods

In a cross-sectional, observational study we are assessing patients’ needs and preferences towards the treatment options of the planned RCT “Surgery as needed versus surgery on principle in patients with post-neoadjuvant complete tumor response of esophageal cancer (ESORES)” in two consecutive phases: (1) A development phase and (2) a pilot testing phase.

We start with detailed qualitative patient interviews (*n* = 10–15) in the development phase. Patients who had already undergone nCT or nCRT for EC and partially also surgery are asked for their needs, preferences, and attitudes towards choice of treatment. Particularly, patients are asked regarding their potential willingness to participate, to accept randomization, and to comply with the treatment to which they will be allocated.

Additionally, *n* = 10 medical experts in the field of EC treatment (i.e., 3–5 clinicians out of the field of EC treatment, 3–5 nurses, and psycho-oncologists) are asked regarding their experiences with patients in terms of patients’ attitudes towards treatment choices, preferred treatment option, and the reasons for it.

With respect to patient participation, *n* = 2 members of an adequate Peer-Support Organization (18) are asked to review the interview guidelines, the interview statements, and the provisional PDAQ, and to give comments on them.

Based on the information regarding patients’ goals and attitudes, peer-support group members and medical experts’ attitudes, the final PDAQ will be constructed. In the subsequent pilot phase, *n* = 120 patients with EC after nCT or nCRT are asked to fill in the PDAQ in a multicenter trial in order to develop patient-centered trial information to serve as study material in the envisaged RCT. The specific study phases are depicted in **Table 1**. Furthermore, details about the study procedures of the pilot phase are provided in **Figure 1**.

**Table 1 T1:** Study procedures.

Phase	Study Procedures
**Development phase (0–7 months)**	Interview guideline
	Patient eligibility
	Enrollment, study information, and informed consent
	Disease specific treatment data of study condition (EC)
	Interviews
	Patients in individual interviews (*n* = 10–15)
	Medical experts (*n* = 10)
	PDAQ
	Development
	Pre-testing (*n* = 10 patients; *n* = 2 patients advocates)
	Adaption
**Pilot phase (8–20 months)**	PDAQ Survey (*n* = 120 patients including)
	Age
	Gender
	Education
	FoP-Q-SF
	PHQ-9
	GAD-7
	EORTC-QoL-C30
	OES18
	Trial information material
	Disease specific treatment data of study condition (EC)

PDAQ, Preference and Decision Aid Questionnaire; FoP-Q-SF, Fear of Progression Questionnaire Short-Form; PHQ-9, Patient Health Questionnaire-9; GAD-7, Generalized Anxiety Disorder Screener-7; EORTC-QoL-C30, European Organization for Research and Treatment of Cancer’s Core Quality of Life Assessment; OES18, Oesophageal short module of the EORTC questionnaire.

**Figure 1 f1:**
[figure not shown]
Flow Chart.

### Participants

In the development phase patients’ screening for trial eligibility will be performed at the Medical Center University Freiburg. In the pilot phase the PDAQ survey will be performed multicentric in total five specialized centers in Germany. Eligible patients according to the inclusion criteria will be identified through medical records and will be patients after neoadjuvant treatment and before or after surgery. Patients, who participated in the pilot phase, will not participate in the consecutive RCT.

Patient participation in the study is voluntary and patients can withdraw their consent to participate at any time during the study without incurring disadvantages in treatment. Patients will be given sufficient time to read and understand the study information, to review the information, ask questions, and receive satisfactory answers from the trial physician. Subsequently, patients will be asked to sign the informed consent after completed information process. Patients eligible to participate in the study (development phase and pilot phase) have to fulfill the following inclusion criteria:

#### Exclusion Criteria

Patients who meet the following exclusion criteria cannot participate in the trial:

No written consent available.Patients with gastric cancer.Patients with tumors of the cervical esophagus.Co-morbidity with contraindication for esophageal surgery.Patient without legal capacity who is unable to understand the nature, significance, and consequences of the study.Concurrent medical or psychiatric condition that might preclude participation in the study according to investigator assessment.Cognitive or other type of impairment (such as severe psychiatric disorders and severe cognitive disorders that would interfere with completing paper-pencil questionnaires).Simultaneous participation in other studies which could interfere with this study and/or participation before the end of a required restriction period.

### Study Procedures

#### Development Phase

Patients’ will be asked to provide basic demographic data regarding age, gender, ethnicity, highest level of education, employment status, and marital status. Medical data such as current health status (Eastern Cooperative Oncology Group [ECOG] performance status), time since diagnosis, tumor type (adenocarcinoma, squamous cell carcinoma), clinical stage (cT/cN category), pathological stage (pT/pN category and tumor regression staging), and previous and actual medical treatment is taken from the medical documentation.

Based on patient preferences identified from literature review and expert opinion, relevant issues will be phrased for structuring the interviews.

For patients to be able to evaluate treatment options, they need to have adequate knowledge of treatment opportunities and realistic expectations of potential benefits and harms. Therefore, the interviews assessing patients’ treatment preferences, could start by repeating the information about both the “surveillance and surgery as needed” and the “surgery on principle” procedures including a detailed description of respective advantages and disadvantages. It should be stressed, that it is unknown which of the two procedures is superior and that the advantage of the “surveillance and surgery as needed” method is that post-treatment recovery might be quicker and less impairment of long-term HRQoL might be apparent. The advantage of the “surgery on principle” procedure might be improvement of local tumor control and, therefore, improved disease-free survival and the possibility for pathohistological examination of the surgical specimen (19).

Even though patients have no choice of treatment in an RCT, it is important to evaluate their expectations regarding treatment choice along with their constraints regarding RCT. Therefore, the interview guide includes patients’ concerns of clinical trials that might be:

Feeling “left out” and cannot decide by myself which treatment I would like to choose (in a RCT)Feeling emotionally challenged in the expectation maybe not to be randomized in to my preferred treatment armFeeling satisfied to be part of medical research that can help improving my or other patients’ treatment situation in the futureI prefer taking part in a clinical trial, to be one of the first people to benefit from a new treatment, knowing there’s also a chance that the new treatment turns out to be no better, or worse, than the standard treatment

The interview will end with the question: “If you are randomly assigned to group A, would you accept the assignment or request a group change?”

The individual patient interviews will explore additionally patients’ need for information, their expectations regarding treatment, their subjective experiences, and their individual actions regarding decision making.

Surgeons/medical experts might also have treatment preferences that hinder the study information process and might contribute to recruitment bias. Therefore, medical experts/recruiters of the planned centers are asked regarding their attitudes towards both treatment options to ensure that they objectively inform patients about risks and benefits. Further the specialists are asked to focus on two basic questions: (a) are issues included in the preliminary study information material which they consider irrelevant for this patient group and if so, why do they consider these issues irrelevant? and (b) are there issues missing from this information material that the specialists consider relevant and if so, why do they consider these issues relevant?

A project team member with experience in qualitative research methods will conduct the interviews with patients and medical experts (i.e., 3–5 clinicians out of the field of EC treatment, 3–5 nurses, and psycho-oncologists) using the interview guides. Duration of the interviews are calculated approximately 30 minutes. Members from an adequate cancer support group will be asked to provide a review of those gathered views and opinions.

In the development phase, the qualitative analysis of the interviews will lead to a list of issues representing the insights of patients’ preferences towards treatment choice. Both, the qualitative analysis of the patients’ interviews (including former patients from the cancer support group) and the medical experts’ opinion will lead to an adaptation of issues, if applicable. A preliminary PDAQ questionnaire will be developed from the list of issues and 10 patients are asked to give their comments on the phrases using a think-aloud technique. These findings will lead to the final PDAQ with phrased items that can be evaluated for relevance and importance.

#### Pilot Phase

After pretesting the preliminary version of the PDAQ will be revised. The final PDAQ will assess patients’ needs, preferences, and its influencing factors towards the choices of treatment. The results of the questionnaire survey in the pilot testing phase will provide information for adapting the informed consent material to the patients’ needs and preferences for the main study. Patients’ information needs and values identified by the PDAQ will be transferred in the proven format of decision-support to be easy to understand, well-structured, clear, and helpful, which will serve as study information material in the envisaged RCT. The medical expert opinion as well as the review of former patients from the cancer support group are included in developing the study information material.

In the pilot phase, the survey includes the PDAQ questionnaire, captures sociodemographic and medical information and the following standardized instruments:

FoP-Q-SF: The Fear of Progression Questionnaire Short-Form [FoP-Q-SF (20)] is a concise standardized psychological instrument to measure the fear of progression (FoP) in chronically ill patients (cancer, rheumatic diseases, and diabetes mellitus). The questionnaire consists of 12 items and covers the factors: *affective reactions*, *partnership/family*, *occupation*, and *loss of autonomy*.PHQ-9: The Patient Health Questionnaire-9 [PHQ-9 (21)] is a brief and validated measure of depression severity. It consists of 9 items and covers the 9 depression criteria of the Diagnostic and Statistical Manual of Mental Disorder IV (DSM-IV). For each item, the patient has to choose from 0 (“not at all”) to 3 (“nearly every day”). Thus, the maximum score is 27.GAD-7: The Generalized Anxiety Disorder Screener-7 [GAD-7 (22)] is a standardized 7-item self-report anxiety questionnaire assessing the anxiety symptoms: *nervousness*, *inability to stop worrying*, *excessive worry*, *restlessness*, *difficulty in relaxing*, *easy irritation*, and *fear of something awful happening*. Similar to the PHQ-9, the total score is calculated by adding together the scores for all items ranging from 0 (“not at all”) to 3 (“nearly every day”).EORTC-QoL-C30: The European Organization for Research and Treatment of Cancer’s (EORTC) core quality of life assessment [EORTC-QoL-C30 (23, 24)] is a validated instrument to assess the quality of life of oncological patients. It contains 30 questions in 10 subscales. Furthermore, the EORTC-QoL-C30 has a specific module for EC called OES18 (25) to assess the detailed symptoms of EC-patients.

The survey will be conducted in collaboration with five centers. A final sample of n = 120 patients will be included.

### Trial Information Material

Based on the results of the survey, the information material for the envisaged RCT will be revised. In addition, a check-list for clinicians will be developed to guide the information process.

Recommendations for the design of risk information include graphical displays to increase the effectiveness of risk communication (3); therein simple bar charts are preferred and absolute risks are given rather than relative risks, and comparisons with everyday risks are proposed.

We will base the development of information material on useful design formats that follow the quality standards for patient decision aids for presenting risk information and prediction models [i.e., the SUNDAE (Standards for Universal Reporting of Patient Decision Aid Evaluation) checklist (26), and the IPDAS (International Patient Decision Aid Standard) Collaboration] that include percentiles, ratios, and pictographs (7, 27, 28).

Estimates for OS after nCRT or nCT + esophagectomy can be obtained from an interactive web-based instrument (nomogram), where the individual survival of patients is estimated based on their individual pathological, demographic, and treatment data (29).

It is suggested that clinicians have a toolbox of presentation styles to suit different patients and outcomes (30). It may be that multimodal consultations, incorporating verbal and visual information, presented differently, such as event rates, risk ladders, or bar charts, may maximize patient understanding of different treatment outcomes. Option grid formats can be used to display attributes of treatment options and to answer patients’ most relevant questions (16, 17, 31). Patient-relevant questions when making trade-offs with regard to their treatment decision might be for example:

How long will I stay in hospital? (Risk of in hospital mortality)Which treatment is the best for long-term survival? (5-year survival rate)What are the chances of cancer coming back in the esophagus? (Risk of relapse)How long will it take to recover? (Risk of persistent gastrointestinal problems)How many patients experience physical side effects (e.g., speech pathologies, dysphagia, respiratory restrictions, pain, anxiety, etc.)? (Risk of post-treatment complications)How many consultations will I have? (Burden of appointments)

The trial information material developed and designed during development and pilot testing phase including a clinician’s check-list to guide the information process will be used to provide comprehensive education and information about the randomized controlled trial for patients with non-metastatic EC after nCRT.

### Data Management and Monitoring

During the study, all personal data will be kept separately in the patient identification log (identification of patient and contact details). All patient data will be captured in pseudonymized form. After transcription all audio files will be stored until the end of the project at least for three years and then be deleted. The data management will be performed with REDCap™ Version 9 ([contact]).

Details on data management (procedures, responsibilities, deviations, etc.) will be described in a data management manual which will be continuously updated and maintained during the trial. The technical specifications of the database will be described in a data description plan (DDP). Before any data entry is performed, the trial database and electronic case report forms (eCRFs) will be validated. Site data entry personnel will not be given access to the trial data base until they have been trained and signed an access form.

Statistical Analysis System (SAS) software will be used to review the data for completeness, consistency and plausibility. The checks to be programmed will be specified beforehand in a data validation plan. After running the check programs, the resulting queries will be sent to the investigator for correction or verification of the documented data. Data corrections will be entered directly into REDCap by the responsible investigator, or designated person. Query forms which contain the corrections must be confirmed by the dated signature of the investigator (not the study nurse) in the designated places. Due to the characteristics of the study, no data monitoring committee (DMC) will be included.

### Biostatistical Planning and Analysis

#### Development Phase

In this phase the focus lies on qualitative analyses of the patient interviews supported by specific software (MAXQDA). Statistical analyses are confined to descriptive analyses. All qualitative analyses will be performed at the Endowed Professorship Self-help Research, Interdisciplinary Tumor Center Medical University Freiburg, with the support of the Clinical trial unit if applicable.

#### Pilot Phase

The pilot phase mainly has two objectives:

1) The development of patient-centered information material optimally fulfilling the individual needs of the patients with the aim to improve the recruitment of patients for the clinical trial and to improve their consent to randomization between the standard treatment “surgery on principle” and the experimental treatment “surveillance and surgery as needed” and their adherence to the randomized treatment.

2) To verify assumptions for sample size calculation for the planned RCT regarding the rate of EAC vs. ESCC, the rate of nCRT vs. nCT, and the pCR rate after surgery.

With regard to objective 1) the effects of socio-demographic, disease-specific, and psycho-social factors on patients’ treatment preference (“surgery on principle” versus “surveillance and surgery as needed”) will be analyzed. Additionally to descriptive analyses, univariate and multivariate logistic regression models will be used to identify which factors may be associated with patients’ treatment preference. Effect sizes will be quantified by odds ratios with 95%-confidence intervals and tested using the Wald test. P-values will be interpreted in a descriptive sense. Those factors identified as influential with a relevant effect size will then especially be considered in the development of the patient-centered trial information material and check-list for clinicians in the planned RCT.

Sample size was chosen based on feasibility without formal sample size planning based on statistical power calculations. The inclusion of 120 patients from 5 clinical centers within a time period of 6 to 12 months was regarded as feasible. The following statistical consideration only exemplifies the possible conclusions with the chosen sample size: 120 patients would provide 80% power for an identification of a factor influencing patients’ preference with an odds ratio of 3 at a significance level of.05, considering adjustment for other correlated factors (variance inflation factor 1.2). With regard to objective 2) descriptive analyses of tumor type, type of neoadjuvant therapy, and of pCR status after surgery will be performed.

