Considering the clinical relevance of identifying factors influencing patients’ decision towards one treatment option, it is important to mention specific problems with adherence to the allocated trial treatment in completed RCTs comparing surveillance with surgery on principle in EC patients (17, 32, 33). In the published trials, a striking difference in the compliance to the allocated treatment was to be noticed between the different arms of the trials, with higher rates of non-compliance to the protocol in the surgical-arms. For the ongoing SANO-trial, this factor was included to the study design by using a cluster-randomisation (13). For the planned RCT, we are going to address this issue not alone by specific trial design but also by conducting this pilot study to create patient-centered trial information material. The eligibility criteria of the main trial won`t be affected by the results of the patient’s participation study. The study aims to optimize information material for the main trail we expect that this shall improve study recruitment and protocol adherence by creating comprehensive and patient-centred study information material.

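### The named Wald test is a weak choice at 120 patients for uncommon factors that point towards the majority preference, and it fails at an empty cell; a minor, cheap fix

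*Protocol article*

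**What the plan says.** Under Biostatistical Planning and Analysis, Pilot Phase, the first objective is served by regression: "univariate and multivariate logistic regression models will be used to identify which factors may be associated with patients’ treatment preference". The outcome is binary: surgery on principle, or surveillance with surgery as needed. On estimation and testing the text says: "Effect sizes will be quantified by odds ratios with 95%-confidence intervals and tested using the Wald test". Wald is attached to the test; no method is attached to the interval, and no fallback is given for sparse data.

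Two sentences govern how the results are used. One reads "P-values will be interpreted in a descriptive sense". The other is the carry-forward rule: "Those factors identified as influential with a relevant effect size will then especially be considered in the development of the patient-centered trial information material". No significance threshold appears in that rule.

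On size, the article says "Sample size was chosen based on feasibility without formal sample size planning based on statistical power calculations". An illustration follows, computed for a 5% level and a variance inflation factor of 1.2: "120 patients would provide 80% power for an identification of a factor influencing patients’ preference with an odds ratio of 3". The article states neither a preference split nor a factor prevalence.

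**The concern.** The Wald statistic divides the estimated log odds ratio by its standard error. In logistic regression the standard error can grow faster than the estimate as one cell of the table empties, so the statistic can shrink while the association strengthens. At an empty cell the estimate runs to infinity, the standard error becomes huge, and the p-value approaches 1.

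The analysis is meant to find factors linked to preference so that the information material and the clinicians' check-list can address them. A small subgroup that is nearly unanimous for the more popular option is such a finding, and the named test would print a p-value suggesting no evidence. A descriptive p-value should still describe the data.

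**Working it through.** **Inputs.** From the article: N = 120, odds ratio (OR) 3, level 0.05 (two-sided assumed), variance inflation factor 1.2. Assumed, because the article gives no figure: preference split from 50:50 to 85:15, and a binary factor held by 20% to 50% of patients.

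**1. The article's own power figure.** Power = Φ(√(N/VIF · P(1−P) · B(1−B)) · ln OR − 1.96), with P the preference split and B the factor prevalence. N/VIF = 120/1.2 = 100. At P = B = 0.5: √(100 × 0.25 × 0.25) = 2.5; 2.5 × ln 3 = 2.747; 2.747 − 1.96 = 0.787; Φ = 78.4%. That reproduces the stated 80% to within 2 points. With B = 0.5 the same formula gives 76.8% at a 60:40 split and 71.1% at 70:30. The illustration therefore fits a near-even split and a common factor, which is where the choice of test makes no difference (step 3).

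**2. Two example tables** (patients choosing the minority option, factor present vs absent).

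- 1/30 vs 17/90: ln OR = ln[(1 × 73)/(29 × 17)] = −1.91; SE = √(1/1 + 1/29 + 1/17 + 1/73) = 1.05; Wald p = 0.069. Likelihood-ratio p = 0.020.
- 0/30 vs 24/90: the Wald SE is about 14,500, p = 0.999, and a Wald interval would run from 0 to infinity. Expected counts are 6, 24, 18 and 72, so the likelihood-ratio statistic is 2[30 ln(30/24) + 24 ln(24/18) + 66 ln(66/72)] = 15.7, p = 0.00007. Firth's method gives OR 0.045, profile interval 0.0003 to 0.34, p = 0.0004.

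**3. Exact univariate power at N = 120.** The two probabilities of choosing the minority option, p1 (factor present) and p0 (absent), are solved from B·p1 + (1−B)·p0 = minority share and odds(p1)/odds(p0) = 1/OR when the factor points to the majority. All 2×2 tables are then enumerated with binomial weights, an empty cell counting as no Wald rejection. For 75:25, B = 20%, OR 3: p1 = 0.1165 and p0 = 0.2834, so 24 × 0.1165 = 2.8 patients are expected in the sparse cell, which is empty with probability (1 − 0.1165)^24 = 5%.

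| Split | Factor held by | OR and direction | Wald | Likelihood ratio |
|---|---|---|---|---|
| 50:50 | 50% | 3 | 85.5% | 85.5% |
| 70:30 | 50% | 3 | 76.5% | 77.6% |
| 75:25 | 50% | 3 | 70.9% | 72.5% |
| 80:20 | 50% | 3 | 62.8% | 65.6% |
| 65:35 | 30% | 3, to majority | 67.5% | 70.5% |
| 60:40 | 20% | 3, to majority | 55.3% | 59.8% |
| 75:25 | 20% | 3, to majority | 24% | 45% |
| 75:25 | 20% | 5, to majority | 39% | 72% |
| 85:15 | 20% | 3, to majority | 1% | 33% |
| 75:25 | 20% | 3, to minority | 61.4% | 60.6% |
| 85:15 | 20% | 3, to minority | 50.1% | 48.3% |

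In the 85:15 row pointing to the majority, a cell is empty in 20% of samples.

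**4. Adjusted models.** Simulations with five other covariates give the same picture for a 20% factor pointing to the majority. At 75:25 and OR 3, power is 27% (Wald), 47% (likelihood ratio) and 38% (penalised likelihood ratio). Type I error is 3–4%, 6–7% and 4–5% respectively.

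**The case against.** The case for leaving the sentence alone is substantial.

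- **The interval.** A reader might infer that Wald intervals are fixed too and that unbounded intervals are planned. The text names Wald for the test only, so that reading is unsupported.
- **The consequence.** A reader might infer that strong factors would be dropped from the information material. The article does not say so: p-values are descriptive, selection refers to a relevant effect size, and descriptive analyses are planned alongside. A 0/30 against 24/90 pattern would be plain in a cross-table. This limits the harm considerably. What remains is that the printed p-value would contradict the table, and that under separation the maximum-likelihood odds ratio is infinite and cannot be weighed as an effect size.
- **The skewed split.** A reader might take the Discussion's remark that "a striking difference in the compliance to the allocated treatment was to be noticed between the different arms of the trials" as evidence of lopsided preference. It concerns adherence after randomisation in earlier trials, not stated preference in this survey, which recruits patients before and after surgery. The skew stays an assumption.
- **Direction and prevalence.** The loss is not general. It vanishes when the factor points to the minority option and is small for common factors. Age and the questionnaire scores, if analysed as scores, have no two-by-two cell to empty.
- **Unequal test sizes.** Part of the gap arises because the plain likelihood-ratio test runs above 5%. Against the penalised version, the adjusted gap at 75:25 and OR 3 is 38 − 27 = 11 points rather than 47 − 27 = 20.
- **Place in the documents.** Handling of separation may sit in an analysis plan that is not shown. The test itself, however, is named here, and that choice can be questioned.

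**Conclusion.** The point stands as a minor one. The article commits every preference model to a test that, at 120 patients, is weak for uncommon factors pointing to the majority option and uninformative at an empty cell. At an assumed 75:25 split and 20% prevalence, about 21 points of univariate power are lost at an odds ratio of 3 (45 − 24) and 33 at an odds ratio of 5 (72 − 39). For a 50% factor at an odds ratio of 3 with splits up to 80:20, the loss is 0 to 3 points. The size thus depends on a split and a prevalence that the article does not give. The exploratory use of the p-values keeps the practical consequence small.

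**What to change.** In the Pilot Phase paragraph, replace the clause naming the Wald test so that odds ratios are *tested with the likelihood-ratio test and reported with 95% profile-likelihood confidence intervals; where a cell is empty or separation occurs, penalised-likelihood (Firth) estimates, tests and intervals are used*. The Firth part is needed because changing the test alone leaves the odds ratio infinite at an empty cell.

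The cost is one sentence and standard software options, with no new data and no change in sample size. The downside is that the plain likelihood-ratio test is slightly liberal in sparse cells: about 6% in the settings above, and up to 8.6% in a very sparse one (80:20 split, factor held by 10%). With descriptive p-values that is acceptable.
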